### Data analysis

Analysis and reporting will adhere to CONSORT 2010 guidelines extension for feasibility trials [22]. A CONSORT flow diagram will be used to display data completeness and resident throughput from eligibility screening, invitation, study acceptance, and final follow-up visit. Feasibility figures on recruitment and retention, COG-D completion, adherence to COG-D implementation protocol, outcome completion rate, and adverse event will be reported and checked against the pre-defined progression criteria.

Signals of efficacy will be analysed in resident and staff candidate outcome measures. Proposed outcome measures (residents: CMAI [23, 24], QUALID [25], BADLS [26], FAST [20], and EQ-5D-5L [27]; care-staff: SCIDS [28], CBI [29], and COG-DQ [15]) will be summarized at baseline, 6-month, and 9-month follow-up. Calculated effect sizes of candidate outcome measures (CMAI, QUALID, and the BADLS), and their corresponding intraclass correlation coefficients (ICCs), will be employed to establish the primary endpoint and sample size for the future definitive cRCT. The calculated completion rates of study measures and questionnaires will be utilized, with their burden and acceptability, to inform the choice of study outcomes for a future large-scale cRCT.

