## Objectives

### Primary objective

To investigate the feasibility of conducting a future large-scale cluster RCT (cRCT) to assess the effectiveness and cost-effectiveness of the Cognitive Daisy (COG-D) intervention in care homes. Feasibility of a future cRCT will be investigated with regard to the following areas of uncertainty: (1) recruitment and retention of care homes, residents and care-staff in both intervention and control conditions, (2) adherence to COG-D intervention protocol, (3) acceptability and data completion rates of the candidate outcome measures, (4) estimates of effect sizes of proposed outcome measures to establish primary endpoint and sample size for the future CRT, (5) ability to collect health economic data required to undertake a cost-effectiveness analysis in the definitive trial.

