### Sample size

In line with recommended sample sizes for feasibility studies [18], the aim is to recruit 70 care home residents (35 per arm). To accommodate 30% loss to follow up, 100 residents will be recruited. This sample size will allow for reliable estimation of key feasibility figures, e.g., the 95% confidence interval on retention rate will have the width of ± 9%. To ensure that the target recruitment rate of residents can be achieved from 8 to 10 care homes (it is expected that on average ~ 40–60% of residents will be recruited), only care homes with a minimum of 20 beds will be considered eligible (no maximum limit will be used). We aim to recruit 50 members of staff and will report on the feasibility of recruiting staff for the COG-D intervention.

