#### Feasibility outcomes

Recruitment and retention of care homes, residents, and care-staff in both intervention and control conditions will be calculated to inform the number of care homes needed to achieve the target sample size for a future definitive trial. Acceptability, fidelity, and adherence to COG-D intervention protocol will be evaluated with completion rates for staff training and COG-D assessments, use and display of Daisies and revisions to care-plan based on COG-D assessments.

Feasibility of a Health Economic assessment will be explored in the ability to collect the data required (COG-D use, resource use, health and quality of life of residents) to undertake a cost-effectiveness analysis in the definitive trial and estimate potential costs and health benefits of the intervention.

Demographic data for residents (age, ethnicity, length of time in care home, gender, dementia diagnosis) will be collected from care plans. For staff, data will be obtained as part of the anonymous staff questionnaire (further training completed, duration of employment at care home) or in a short questionnaire preceding the staff training (role in care home, ethnicity (to explore diversity), age category, gender).

Candidate outcome measures for residents (by proxy) will be collected in interviews with researchers and staff outcomes are collected in the anonymous staff questionnaire (self-completed). Data completion rates of the candidate outcome measures (at each time point) will be calculated to determine which is the most appropriate primary outcome, agree other study measures and inform sample size calculation for the definitive trial.

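### Observed effect sizes and ICCs from 8–10 homes are made a basis for the definitive trial's primary endpoint and sample size, which they are too imprecise to support

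*Protocol article*

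**What the plan says.** The Primary objective of the Protocol article lists five areas of uncertainty. The fourth is "estimates of effect sizes of proposed outcome measures to establish primary endpoint and sample size for the future CRT". The Data analysis section names the measures, "Calculated effect sizes of candidate outcome measures (CMAI, QUALID, and the BADLS", adds their intraclass correlation coefficients, and says that these quantities "will be employed to establish the primary endpoint and sample size for the future definitive cRCT".

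Other inputs are named too. Under Feasibility outcomes, data completion rates "will be calculated to determine which is the most appropriate primary outcome, agree other study measures and inform sample size calculation for the definitive trial". The Data analysis section adds that completion rates "will be utilized, with their burden and acceptability, to inform the choice of study outcomes for a future large-scale cRCT". No order of precedence or weighting between these inputs and the effect sizes is given.

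The Sample size section says "the aim is to recruit 70 care home residents (35 per arm") and then "To accommodate 30% loss to follow up, 100 residents will be recruited". The only precision it claims is ±9% for the retention rate. The homes number 8 to 10 (Study setting), allocated 1:1 (Trial design), so there are 4 or 5 per arm.

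**The concern.** The study exists to inform a definitive cluster trial, and the endpoint and sample size are two of its main products. The sample was sized for feasibility proportions, not for between-arm effects or ICCs. An observed effect from a handful of homes is mostly sampling error. Used to compare three measures, it may favour the one that happened to do well. Used as the target difference, it carries that error into the next trial's power. The second problem remains even if the endpoint is fixed in advance, because completion, burden and acceptability supply no target difference.

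**Working it through.** **The plan's own figures.** 70 / (1 − 0.30) = 100 recruited. Retention half-width: 1.96 × √(0.7 × 0.3 / 100) = 0.090, the stated ±9%. Both reproduce. This is simple random sampling for a proportion and says nothing about effects or ICCs.

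**Inputs.** From the document: 35 analysed residents per arm and 8 or 10 homes, so m = 70/8 = 8.75 or 70/10 = 7 analysed per home. Assumed, because the document gives none: ICC 0.05–0.10, correlation between outcomes 0.3–0.5, two-sided 5% tests.

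**Precision of one standardised effect.** SE = √[(2/35) × DE], with DE = 1 + (m − 1) × ICC.

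| Homes | ICC | DE | SE | 95% half-width (z) |
|---|---|---|---|---|
| 10 | 0.05 | 1.30 | 0.273 | 0.53 |
| 8 | 0.05 | 1.39 | 0.282 | 0.55 |
| 10 | 0.10 | 1.60 | 0.302 | 0.59 |
| 8 | 0.10 | 1.78 | 0.318 | 0.62 |

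Using t with (homes − 2) degrees of freedom, the two ICC 0.05 rows become 0.63 and 0.69. With an assumed baseline correlation of 0.7 at both levels, SEs are multiplied by √(1 − 0.49) = 0.714. The range of z half-widths is then about 0.38 to 0.45. With all 100 residents analysed and no clustering, the half-width would still be 1.96 × √(2/50) = 0.39.

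**What that means for sizing.** Suppose 0.3 SD is observed (8 homes, ICC 0.05). The interval is 0.30 ± 0.55, or −0.25 to 0.85. For 80% power, n per arm before clustering is 2 × (1.96 + 0.84)² / d². This gives about 175 at 0.3 and about 22 at 0.85. No finite number corresponds to the part of the interval at or below zero.

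**Precision of the ICC.** With θ = 1 + m × ICC / (1 − ICC), the ANOVA estimate is zero or below when an F variable on (homes − 2, 70 − homes) degrees of freedom falls below 1/θ. At a true ICC of 0.05:
- 8 homes: θ = 1.46, probability 0.34.
- 10 homes: θ = 1.37, probability 0.34.
- The upper 97.5% point of the estimate is 0.24 and 0.25 respectively.

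**Worst-case illustration of selection.** Suppose the measure with the largest observed effect were chosen and all three true effects were 0.2 SD. The expected maximum of three equally correlated normal estimates is 0.2 + 0.846 × SE × √(1 − ρ).
- Low end (SE 0.273, ρ = 0.5): 0.2 + 0.163 = 0.36.
- High end (SE 0.318, ρ = 0.3): 0.2 + 0.226 = 0.43.
- With the baseline adjustment above, the excess is multiplied by 0.714, giving 0.32 to 0.36.

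Power of a next trial designed with 90% power for the chosen effect, when the truth is 0.2:
- Designed for 0.38: Φ[(1.96 + 1.2816) × 0.2/0.38 − 1.96] = Φ(−0.25) = 0.40.
- Designed for 0.32: Φ[(1.96 + 1.2816) × 0.2/0.32 − 1.96] = Φ(0.07) = 0.53.

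**Without selection.** In simulation, the next trial was sized for 80% power on the observed effect and estimated ICC of a single prespecified outcome. Assumptions were true effects of 0.2–0.4 SD, ICC 0.05–0.10, 10 analysed residents per home in the next trial and no baseline adjustment. Its true power fell below 80% in about 53–69% of runs with a positive observed effect.

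**The case against.** Several stronger readings are tempting, and the document does not support them.

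- **That the largest observed effect wins.** No section says so. Effect size is one input beside completion, burden and acceptability, so the best-of-three figures are a worst case for the wording, not its consequence.
- **That the effect-size and completion inputs conflict.** They can all be used together. The fault is that their weighting is unstated.
- **That the ICC estimate pushes the next trial towards too few homes.** It is imprecise in both directions. In simulation the estimate, set to zero when negative, averages about 0.06 for a true 0.05 and exceeds the truth in about 43–45% of runs.
- **That the ranking is pure noise.** Equal true effects make it so by construction. If one measure truly had 0.4 SD and two had 0.2 (8 homes, ICC 0.05, outcome correlation 0.3–0.6), the largest observed effect would identify it in 59–67% of runs, against 33% by chance.

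Baseline data are collected, and adjusting for them would narrow the intervals and soften the power loss, as shown above. Reporting effects and ICCs is ordinary in a feasibility trial, and an analysis plan that is not shown may say how uncertainty will be handled.

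These points limit the size of the problem. They do not remove it. The use of observed effects to establish endpoint and sample size is stated twice, once as part of the primary objective. No important difference or outside ICC is named beside it.

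**Conclusion.** The point stands in a limited form. Observed effect sizes and ICCs are a stated basis for two decisions that this design cannot inform reliably. The 95% half-width for one effect is about 0.53–0.62 SD unadjusted, or about 0.38–0.45 SD with baseline adjustment. About a third of ICC estimates would be zero or below at a true value of 0.05. These sizes rest on the assumed ICC range of 0.05–0.10 and, where used, the assumed baseline correlation of 0.7. The loss to 40% or 53% power also assumes selection of the largest effect and equal true effects of 0.2 SD, and is illustrative only.

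It should be fixed but is not critical to this trial. A reader might infer that the feasibility conclusions are at risk, but none of the progression criteria in Table 2 uses an effect size. The harm would fall on the definitive trial.

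**What to change.** Reword item (4) of the Primary objective and the corresponding sentence of the Data analysis section so that observed effect sizes are no longer a basis for endpoint choice or sample size. In their place:

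- **Endpoint:** choose on relevance, completion, burden or acceptability, and floor or ceiling behaviour.
- **Sample size:** use a justified important difference, this trial's SD and retention with their uncertainty, and an ICC supported by external care-home data. Use this trial's ICC and its confidence interval as a check.
- **Effect estimates:** report with confidence intervals, as descriptive only.

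The cost is wording; data collection is unchanged. The downside is that the target difference and the ICC must be justified from outside this trial.

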#### Process evaluation

Qualitative data will be analyzed using Framework Method of thematic analysis [30], which provides a systematic model for mapping and managing data. It is ideal for analysis that seeks to reduce large amounts of textual data to analyse by case (care home) and code (area of interest) both within and across cases. It includes seven stages transcription, familiarization, coding (inductive and deductive), developing and analytic framework, applying the analytic framework, charting data into the framework matrix and interpretation.

### Safety monitoring

Adverse and serious adverse events will be recorded and reported in accordance with the HHTU SOP for Adverse Event Reporting for non-CTIMPs and will be in accordance with ICH GCP and the Research Governance Framework 2005. There are no serious adverse events anticipated with participating in this Study. Any adverse events will be recorded in participants’ data collection forms (CRFs) using the adverse event report form and in the care home record.

The care home manager/nominated lead will assess the relationship of each event to the study intervention and classify it as either unrelated or related to the intervention. All adverse events will be recorded and closely monitored until resolution, stabilization, or until it has been shown that the study intervention is not the cause. All AEs will therefore be followed-up until the event has resolved or a decision has been taken for no further follow-up.

As deaths are expected within the trial population, they will not be subject to expedited reporting to the main REC, unless the frequency of deaths observed within the trial population is significantly higher than that expected in the general population. All deaths occurring from the date of consent up to the last data collection visit will be highlighted to the study researcher by the care home (within a week of becoming aware). Death reports will be reviewed by the Chief Investigator monthly and presented at TMG meetings. The Trial Steering Committee (TSC) and Sponsor will be informed of deaths on a regular basis. Reporting of deaths will support avoidance of inappropriate contact by the researchers with the resident’s family following a death. The researcher will contact the care home to ascertain resident status prior to any contact with a relative/friend.

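### The exemption of deaths from expedited ethics reporting takes no account of causality, so as written it also covers a death classed as related to COG-D

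*Protocol article*

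**What the plan says.** All of the relevant text is in the Safety monitoring section of the protocol article.

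- **General rule.** Adverse and serious adverse events follow the trials unit's SOP for non-CTIMPs. The SOP is cited but not reproduced.
- **Expectation.** "There are no serious adverse events anticipated with participating in this Study".
- **Causality.** The care home manager or nominated lead assesses each event and must "classify it as either unrelated or related to the intervention".
- **Deaths.** Because deaths are expected in this population, "they will not be subject to expedited reporting to the main REC", with a single exception: "unless the frequency of deaths observed within the trial population is significantly higher than that expected in the general population".
- **Timing for deaths.** The care home tells the study researcher within a week of learning of the death. After that, "Death reports will be reviewed by the Chief Investigator monthly and presented at TMG meetings". For oversight bodies, "The Trial Steering Committee (TSC) and Sponsor will be informed of deaths on a regular basis".

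**The concern.** The exemption rests on background mortality: older care home residents die during a trial of this length for reasons unconnected with it, and sending each such death to the ethics committee would serve no purpose. That argument covers deaths unrelated to the intervention. It gives no reason to exempt a death that the responsible person has classed as related. Because the section anticipates no serious adverse event from taking part, a related death would be unanticipated on the protocol's own terms.

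The rule nevertheless applies to deaths as a class. Its one exception is a count, which a single death cannot trigger because of its cause. This is separate from whether the general population is a suitable comparator: with an ideal comparator, a lone related death would still be exempt.

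What is at stake is oversight. Residents without capacity can be enrolled on a consultee's advice (Recruitment and consent, Residents), so independent ethics review matters here. The Background section says that this study will inform a larger definitive trial, into which the clause could be carried unchanged.

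**Working it through.** **Step 1: does relatedness change the outcome of the death rule?** Applying the sentence and its exception to the four possible cases:

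| Classification of the death | Aggregate death frequency significantly raised? | Expedited to the REC under the death rule? |
|---|---|---|
| Unrelated | No | No |
| Unrelated | Yes | Yes |
| Related | No | No |
| Related | Yes | Yes |

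The last column depends only on the middle one. The classification required earlier in the section has no effect on the death rule.

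**Step 2: how does this sit with the general SOP sentence?** There are two possibilities.

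- The SOP has no separate route for related deaths. Then the exemption stands as in the table.
- The SOP does expedite related serious events. Then the general sentence and the specific death sentence point in opposite directions, and the article does not say which prevails.

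The wording needs correction either way.

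**Step 3: timing.** The article states no total delay, so there is no figure to reproduce. The inputs are the two stated intervals:

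- care home to researcher: up to 7 days from awareness;
- Chief Investigator's review: monthly, taken as 28 to 31 days.

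Maximum delay from the care home's awareness to that review = 7 + review interval:

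- 28-day cycle: 7 + 28 = 35 days (5.0 weeks)
- 30-day cycle: 7 + 30 = 37 days (5.3 weeks)
- 31-day cycle: 7 + 31 = 38 days (5.4 weeks)

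A more typical figure keeps the full week's lag and assumes an average wait of half a mean month (30.44 days): 7 + 30.44/2 = 22.2 days (3.2 weeks).

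The clock starts at the care home's awareness; any time between the death and that point would add to these figures. For the Trial Steering Committee and Sponsor nothing can be calculated, because only regularity is stated.

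**The case against.** The strongest objection is the unseen SOP. The section opens by placing all serious adverse events under it, a death is such an event, and a journal article may leave reporting routes to the SOP or the full protocol. This limits the claim. A reader might infer that a related death would certainly not be expedited; the documents do not support that, because the SOP could override the sentence. The point itself survives: the article does not leave the matter open but states an unqualified exemption and names its only exception.

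A second objection is that the exemption is tied to deaths being expected, so an unexpected related death falls outside its reason and returns to the general rule. That is a possible reading and probably the intended one. But the sentence exempts deaths as a class, and the reader has to supply the limit.

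On timing, a reader might infer that a related death goes unseen for more than five weeks. That is too strong. The 35 to 38 days are a worst case for one routine review, and a 28-day cycle gives exactly five weeks. The care home manager or nominated lead makes the causality assessment, the researcher is told within a week, and nothing forbids earlier escalation. What stands is that the section specifies no study-team review before the monthly one.

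Setting 38 days against a use period of about 183 days (38/183 = 21%) to suggest that a fifth of exposure continues unreviewed adds little. It combines a worst case with one choice of denominator, whereas deaths are tracked from consent to the last data collection visit. Researchers are also in contact with intervention homes through weekly huddles and fortnightly drop-in sessions.

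Nor can one say that the causality assessment has no consequence at all. It bears on how long events are followed up, and the SOP may attach reporting consequences to it.

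Finally, the intervention is staff training, a cognitive assessment and a visual display, so a related death is very unlikely. That is fair, and it keeps the point modest. It also means that the breadth of the exemption saves almost no work.

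**Conclusion.** The point holds in a limited form. As written, the death rule is wider than its rationale: it exempts all deaths from expedited ethics reporting subject only to aggregate frequency, and the related/unrelated classification plays no part in it. A death classed as related would therefore be exempt unless the SOP overrides the sentence, in which case the two conflict. The stated intervals permit at worst about 35 to 38 days to the Chief Investigator's routine review, and about 22 days with an average wait. This assumes that monthly means 28 to 31 days and that the care home uses its full week. The interval for the Trial Steering Committee and Sponsor is not stated.

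The documents do not show that a related death would in practice go unreported. No progression criterion or sample size figure depends on this point. It is a safety-reporting correction that should be made because it is specific and nearly free.

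**What to change.** Limit the exemption to deaths classified as unrelated to the intervention. Then state that any death classified as related is reported to the Chief Investigator and Sponsor on notification and handled under the SOP's reporting route for related serious adverse events. The sponsor should check the SOP when making the change, so that the two texts agree.

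The monthly review can stay for all other deaths. The existing two-way classification can stay too: adding a category for deaths whose relationship cannot be excluded would alter the classification rule itself and is not needed to close this gap.

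The cost is one sentence. Related deaths should be very rare in this trial, so the added reporting burden is close to zero.

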## Discussion

This feasibility study aims to explore the different pathways to impact of COG-D for residents and staff, and to determine to optimal protocol for investigating the effectiveness and cost-effectiveness of COG-D in a future large-scale cRCT in care homes. The inclusion of COG-D re-assessments at the end of the intervention period will provide valuable information about the sensitivity of the Daisies for monitoring change and fluctuations in cognitive functioning of residents with dementia in care homes [7–10]. It will be important to consider these fluctuations in the context of changes in health or medication and to explore the potential combined impact of both factors on independence in daily activities and the optimal way to evaluate this pathway in the future cRCT. Moreover, this information may be valuable for future studies investigating the potential benefits of COG-D in other social care settings and for supporting people with dementia living independently in the community and their family members.

Senior staff who complete the Advanced Training will be invited to lead the COG-D re-assessments with the residents. The proportion of senior staff who choose to accept this role (including facilitators and barriers thereof) will provide important information for further development of the optimal training protocol for the future large-scale RCT. Moreover, feedback from senior staff on the advanced training (in the post-training questionnaire) and their experiences in conducting COG-D assessments (post-trial interviews) will be instrumental in the development of train-the-trainer based training protocol to facilitate larger-scale dissemination of the COG-D package in care homes and other health and social care settings.

